### Administration of treatment

The IVIG or placebo infusion will be given according to the manufacturer's instructions, over about 4–6 hours. A second, similar, dose will be given at or around 48 hours after the first dose. No further IVIG or placebo should be given, in this or any subsequent episodes of sepsis.

### Neonatal management

All other aspects of neonatal management will be left to the discretion of the paediatrician responsible for care. No special investigations and no delays of discharge will be required.

### Measurement of Outcome

#### Primary outcome measure

1. Mortality or major disability at two years, corrected for gestational age

#### Secondary short term outcomes

2. Mortality, chronic lung disease or major cerebral abnormality before hospital discharge, significant positive culture after trial entry, pneumonia, necrotising enterocolitis, duration of respiratory support

#### Secondary long term outcomes

3. Mortality before two years, major disability at 2 years, non-major disability at 2 years

#### Health service utilisation

4. Length of hospital stay and number of hospital admissions

### Data Collection

Hospital mortality, chronic lung disease, major cerebral abnormality and length of stay will be assessed from case notes. Major disability at two years will be assessed by questionnaires sent to the child's parents and health care professionals. Major disability will be defined according to the criteria set out in the National Perinatal Epidemiology Unit (NPEU) and Oxford Regional Health Authority document and will include any major disability in the following domains: neuromotor function, seizures, auditory function, communication, visual function, cognitive function and other physical disability [56,57].

The parental questionnaire incorporates the parent report component of the Parent Report of Children's Abilities (PARCA), which was used in the 2 year follow up of the MRC funded UKOS trial [58]. This shortened version of the PARCA was acceptable to parents, with a high response rate in UKOS, and is currently being validated by the UKOS team. The PARCA score (both parent report and parent administered components) has been validated and was found to predict performance on the Mental Development Index of the Bayley Scales of Infant Development II [58,59]. The overall score for the modified PARCA will give a measure of verbal and non-verbal cognitive abilities. The parents' questionnaire also includes questions about temperament, which may give an early indication of behavioural and attentional difficulties, and also includes questions about respiratory function, hearing, vision, hospital admissions, relevant diagnoses and current function in a number of domains, allowing categorisation of disability as major or non-major.

Experience of other trials in this area at the NPEU, Oxford and elsewhere, suggests that it is possible to determine early neonatal events for all babies recruited. Loss to follow-up after hospital discharge of the child is more problematic.

There are likely to be few children who cannot be traced in the UK either through the hospital of recruitment or the NHS Central Register. Similar high rates of follow-up will be expected in countries participating outside the UK.

### Analysis

An intention to treat analysis will be performed comparing the outcome of all children allocated IVIG with all those allocated placebo, regardless of what treatment was received, or how complete that treatment was. Statistical analysis will calculate the relative risk of an outcome in the IVIG group compared with the placebo group along with a 95% confidence interval. For subgroup analyses, 99% confidence intervals will be calculated to take account of the number of comparisons.

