**Methods and design:**

A randomised, placebo controlled, double blind trial. Babies with suspected or proven neonatal sepsis will be randomised to receive intravenous immunoglobulin therapy or placebo.

Eligibility criteria

Babies must be receiving antibiotics and have proven or suspected serious infection AND have at least one of the following: birthweight less than 1500 g OR evidence of infection in blood culture, cerebrospinal fluid or usually sterile body fluid OR be receiving respiratory support via an endotracheal tube AND there is substantial uncertainty that intravenous immunoglobulin is indicated.

Exclusion criteria

Babies are excluded if intravenous immunoglobulin has already been given OR intravenous immunoglobulin is thought to be needed OR contra-indicated.

Trial treatment

Babies will be given either 10 ml/kg of intravenous immunoglobulin or identical placebo solution over 4–6 hours, repeated 48 hours later.

Primary outcome

Mortality or major disability at two years, corrected for gestational age.

Data collection

Data will be collected at discharge from hospital and at 2 years of age (corrected for gestation) using a parental questionnaire and a health status questionnaire completed during a face-to-face follow-up appointment with the child's paediatrician.

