### Treatment Allocation

The practical arrangements for random allocation to trial groups will be as simple as possible, based on that used in the ORACLE study [53,54]. Staff will open the next sequentially numbered study pack kept in the neonatal unit, which contains all the materials necessary to give a course of study drug.

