#### Subgroup analyses

Ten subgroup analyses will also be undertaken, stratifying by the factors described below.

1. Birth weight. Infants of very low birth weight (VLBW: < 1500 g) v infants with birth weight ≥ 1500 g

2. Small for gestational age infants (< 10^th ^centile) v infants ≥ 10^th ^centile

3. Gestational age at birth: < 26 weeks, 26+0 to 27+6 weeks, 28+0 to 29+6 weeks, 30+0 weeks or more

4. Gender: male vs female

5. Maternal chorioamnionitis: infants born at < 30 weeks gestation to women with clinical chorioamnionitis v infants born at < 30 weeks gestation with no clinical chorioamnionitis v infants born at ≥ 30 weeks

6. Elevated maternal CRP: infants born at < 30 weeks gestation to women with elevated CRP (> 80 mg/l) v infants born at < 30 weeks gestation with no elevated maternal CRP v infants born at ≥ 30 weeks

7. Preterm birth and duration of membrane rupture: Born at < 37 weeks and membranes ruptured for < 24 hours, 24–48 hours or > 48 hours versus born at ≥ 37 weeks

8. Clinical markers of mortality risk:

(i) Clinical evidence of high mortality risk: looking seriously ill or inactive, and has:

(a) capillary refill time > 3 seconds OR

(b) bowel perforation or definite necrotising enterocolitis OR

(c) prolonged bleeding from puncture sites OR

(d) ventilated, SaO_2_/FiO_2 _ratio or PaO_2_/FiO_2 _ratio consistent with > 15% mortality risk for gestation OR

(e) pH consistent with > 15% mortality risk for gestation. [SaO_2_/FiO_2 _ratio, PaO_2_/FiO_2 _ratio and pH consistent with > 15% mortality risk will be extrapolated from oxygenation and pH data in a prospective cohort of 14,000 infants (UK Neonatal Staffing Study) by methods similar to that used in the development of the MRC funded CRIB score [6]]

(ii) Intermediate mortality risk: not satisfying criteria for high risk, but has:

(a) Total white cell count < 5 × 10^9^/l OR

(b) CRP above 15 mg/l OR

(c) platelet count < 50 × 10^9^/l OR

(d) organism(s) isolated in blood or usually sterile site OR

(e) pneumonia on chest X-ray OR

(f) CSF consistent with bacterial meningitis

(iii) Other: not satisfying criteria for high or intermediate risk

9. Type of infection:

(i) Early onset infection (non-contaminant organisms isolated from culture sent before 48 hours):

(a) group B streptococcal disease

(b) other pathogens

(c) indeterminate aetiology

(ii) Late onset infection (non-contaminant organism isolated from culture sent after 48 hours):

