### Sample Size and Feasibility

Table 4 shows positive blood culture rates (including probable contaminants) in 3,963 consecutive infants of all birthweights admitted to a randomly selected, nationally representative cohort of 54 UK neonatal units between 1st March 1998 and 4th September 1998 in a study of organisation and outcomes of neonatal care funded by the NHS Executive [6].

**Table 4 T4:** Positive blood culture rates

**Number with positive cultures**	**Mortality (all causes)**	**Number with negative cultures**	**Mortality (all causes)**
204/3,963 (5%)	16/204 (8%)	3,759/3,963 (95%)	95/3,759 (2.5%)

Among VLBW infants with positive blood cultures, mortality was 14%. In a North American cohort, mortality in VLBW infants with septicaemia was 21% [7]. Assuming combined rates of mortality and major morbidity of 10–20% for all infants and 20–30% for VLBW infants, Table 5 outlines estimated sample sizes.

**Table 5 T5:** Range of estimated sample sizes

**Mortality or major morbidity in control group**	**Mortality or major morbidity in IVIG group**	**Relative risk reduction**	**Total sample size required to detect difference with 95% confidence**	
			
			**80% power**	**90% power**
30%	26%	13%	4,052	5,392
30%	25%	17%	2,580	3,428
30%	20%	33%	626	824
25%	21%	16%	3,572	4,748
25%	20%	20%	2,266	3,006
25%	15%	40%	540	708
20%	16%	20%	2,994	3,972
20%	15%	25%	1,890	2,502
20%	12.5%	37.5%	810	1,066
15%	12%	20%	4,204	5,582
15%	10%	33%	1,450	1,914
12%	9%	25%	3,408	4,516
10%	7.5%	25%	4,166	5,524

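### The primary relative risk names no baseline covariate; adjusting it for gestational age and sex would add some precision at almost no cost

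*Protocol article*

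**What the plan says.** The primary outcome is binary: "Mortality or major disability at two years, corrected for gestational age". The closing phrase concerns the age at which the child is assessed. It is not a covariate adjustment.

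Under Analysis, the main comparison is by intention to treat: "Statistical analysis will calculate the relative risk of an outcome in the IVIG group compared with the placebo group", with a 95% confidence interval. Subgroups get 99% intervals. No covariate is named, and adjustment is neither adopted nor excluded.

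Under Treatment Allocation: "Staff will open the next sequentially numbered study pack kept in the neonatal unit". No stratification or minimisation by gestation, birth weight or severity is described.

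Under Subgroup analyses, birth weight (item 1) and sex (item 4) are listed, and item 3 reads "Gestational age at birth: < 26 weeks, 26+0 to 27+6 weeks, 28+0 to 29+6 weeks, 30+0 weeks or more".

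Under Sample Size and Feasibility, the planning rates are introduced thus: "Assuming combined rates of mortality and major morbidity of 10–20% for all infants and 20–30% for VLBW infants". The same section gives mortality of 14% in culture-positive VLBW infants, and Table 4 gives 8% in all culture-positive infants.

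**The concern.** Eligibility mixes VLBW infants with larger infants who have culture evidence of infection or are ventilated, so baseline risk will vary within the trial. A relative risk that ignores this variation has a wider interval than one that uses it, and it leaves any chance imbalance in gestation within the estimate. The variables needed are already required for the subgroup tables, so the precision would cost no new data.

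Two things make this worth raising even at 5,000 babies. The Feasibility section calls the event rate imprecise and treats 5,000 as a minimum, and it also allows recruitment to end when funding runs out. And if covariates are named only after the data are seen, a difference between crude and adjusted results becomes a matter of dispute.

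**Working it through.** **1. Which comparison the trial was sized on.** Inputs from Table 5: the control and IVIG rates, 80% and 90% power, and the column heading "Total sample size required to detect difference with 95% confidence". Assumptions: two-sided 5% and 1:1 allocation. The formula per arm, with *d* = p1 − p2 and p̄ the mean rate, is

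n = [1.96·√(2p̄(1−p̄)) + z_power·√(p1(1−p1) + p2(1−p2))]² / d²

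n_c = (n/4)·[1 + √(1 + 4/(n·d))]² (continuity correction)

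For 15% against 12% at 80% power, n = 2,036 and n_c = 2,102, so the total is 4,204, exactly as printed. At 90% power, n_c = 2,791 and the total is 5,582, again as printed. All 26 entries reproduce to within 2 babies. The trial was therefore sized on a crude two-proportion comparison with no covariates.

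**2. Crude power at 5,000 (2,500 per arm).**

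Power = Φ{[√2500·d − 1.96·√(2p̄(1−p̄))] / √(p1(1−p1) + p2(1−p2))}

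For 15% against 12%: (1.5 − 0.947)/0.483 = 1.145, giving 87.4%. The same formula gives 95.8% (20% against 16%), 93.3% (12% against 9%) and 87.9% (10% against 7.5%).

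These figures omit the continuity correction. With it, √2500 becomes 50 − 1/(0.03 × 50) = 49.33, and the 15% against 12% figure is about 86.5%. The gains below are of similar size on either basis.

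**3. Gain from adjustment.** If baseline covariates explain a share R² of outcome variance, the variance of the marginal effect falls by a factor of about 1 − R², and 5,000 babies carry the information of 5,000/(1 − R²). The article gives no R², so these are assumed values:

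| Assumed R² | 5,000/(1 − R²) − 5,000 | Power, 15% v 12% | 95% CI around RR 0.80 |
|---|---|---|---|
| 0 | 0 | 87.4% | 0.695–0.921 |
| 2% | 102 | 88.0% | – |
| 5% | 263 | 89.0% | 0.697–0.918 |
| 10% | 556 | 90.5% | 0.700–0.915 |

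The interval uses a standard error of log RR of √{[0.85/(2500 × 0.15) + 0.88/(2500 × 0.12)]·(1 − R²)}. This is 0.0721 at R² = 0 and 0.0684 at 10%.

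**4. What the protocol's own rates imply.** Rates are given only for VLBW against all infants, so this split is the one that can be tried. With VLBW share *w* (not given, so assumed),

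R² = [w/(1 − w)]·(p_VLBW − p_all)² / [p_all(1 − p_all)]

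- 20% in all, 25% in VLBW: at w = 0.2, R² = 0.25 × 0.0025/0.16 = 0.4%, worth 20 babies. At w = 0.7 it is worth 189.
- 20% in all, 30% in VLBW: at w = 0.2, 79 babies. At w = 0.4, R² = 0.667 × 0.01/0.16 = 4.2%, worth 217. At w = 0.6, 517.
- 15% in all, 25% in VLBW: at w = 0.2, 100 babies. At w = 0.5, 426.

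The planning ranges thus allow anything from about 20 babies to 500 or more. Four gestation bands may explain more or less than this single split. The article gives no event rates by band to settle it.

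**The case against.** The strongest reply is that the point rests on silence. The Analysis section never calls the estimate unadjusted, the allocation description is brief, and a full protocol or analysis plan that is not shown may name covariates or describe balancing. This stands as a limit: a reader might infer that the trial is definitely unstratified and its analysis definitely crude, and the article does not establish either. It does state one analysis without covariates and sizes the trial on the matching crude formula, so a crude estimate is the natural reading.

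A reader might also infer that the planned analysis is biased or the trial underpowered. Neither follows. Randomisation makes the crude relative risk valid, its interval already allows for chance imbalance, and power at 5,000 is 87–96% for the 20–25% relative reductions checked. The stated preference for a simple design is a legitimate choice.

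It is tempting to say that several hundred babies' worth of information is lost. That needs an R² of about 5–10%, or a VLBW share of about 40% or more with a ten-point gap in rates. Other values within the planning ranges give fewer than 100.

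Nor can the mortality-risk category (item 8) be treated as a ready baseline covariate. It includes culture, CSF and X-ray findings that may arrive after randomisation, its oxygenation and pH cut-offs are still to be extrapolated from another cohort, and no special investigations are required, so its components may be incomplete.

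Finally, the article offers no evidence that sex predicts this outcome. It is listed only as a subgroup factor, and its contribution may be small.

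**Conclusion.** The point holds as an efficiency improvement. The one stated analysis of the primary outcome uses no baseline covariate, although gestational age and sex must be recorded anyway and the plan itself treats low birth weight as prognostic.

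The size is modest and conditional. At an assumed R² of 5–10%, power for 15% against 12% rises by about 1.6 to 3.1 percentage points, and the interval narrows by about 2.5% to 5% on the log scale (1 − √0.95 and 1 − √0.90). At 2% the gain is about 0.6 points. These figures assume 5,000 babies, 1:1 allocation, two-sided 5%, complete covariates and the approximate 1 − R² variance rule. The trial's conclusion is unlikely to turn on the change.

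**What to change.** State in the Analysis section, before unblinding, that the primary estimate is a marginal relative risk adjusted for gestational age at birth (the four bands of subgroup item 3) and sex. Obtain it by standardisation, or by modified Poisson regression with robust standard errors, with a 95% confidence interval. Report the crude relative risk beside it. If the analysis plan already does this, a cross-reference is enough.

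Leave out the item 8 mortality-risk category unless it is redefined using only information known before randomisation.

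The cost is a wording change and a short rule for any missing gestational age or sex. No new data are needed and the sample size does not change.

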#### Subgroup analyses

Ten subgroup analyses will also be undertaken, stratifying by the factors described below.

1. Birth weight. Infants of very low birth weight (VLBW: < 1500 g) v infants with birth weight ≥ 1500 g

2. Small for gestational age infants (< 10^th ^centile) v infants ≥ 10^th ^centile

3. Gestational age at birth: < 26 weeks, 26+0 to 27+6 weeks, 28+0 to 29+6 weeks, 30+0 weeks or more

4. Gender: male vs female

5. Maternal chorioamnionitis: infants born at < 30 weeks gestation to women with clinical chorioamnionitis v infants born at < 30 weeks gestation with no clinical chorioamnionitis v infants born at ≥ 30 weeks

6. Elevated maternal CRP: infants born at < 30 weeks gestation to women with elevated CRP (> 80 mg/l) v infants born at < 30 weeks gestation with no elevated maternal CRP v infants born at ≥ 30 weeks

7. Preterm birth and duration of membrane rupture: Born at < 37 weeks and membranes ruptured for < 24 hours, 24–48 hours or > 48 hours versus born at ≥ 37 weeks

8. Clinical markers of mortality risk:

(i) Clinical evidence of high mortality risk: looking seriously ill or inactive, and has:

(a) capillary refill time > 3 seconds OR

(b) bowel perforation or definite necrotising enterocolitis OR

(c) prolonged bleeding from puncture sites OR

(d) ventilated, SaO_2_/FiO_2 _ratio or PaO_2_/FiO_2 _ratio consistent with > 15% mortality risk for gestation OR

(e) pH consistent with > 15% mortality risk for gestation. [SaO_2_/FiO_2 _ratio, PaO_2_/FiO_2 _ratio and pH consistent with > 15% mortality risk will be extrapolated from oxygenation and pH data in a prospective cohort of 14,000 infants (UK Neonatal Staffing Study) by methods similar to that used in the development of the MRC funded CRIB score [6]]

(ii) Intermediate mortality risk: not satisfying criteria for high risk, but has:

(a) Total white cell count < 5 × 10^9^/l OR

(b) CRP above 15 mg/l OR

(c) platelet count < 50 × 10^9^/l OR

(d) organism(s) isolated in blood or usually sterile site OR

(e) pneumonia on chest X-ray OR

(f) CSF consistent with bacterial meningitis

(iii) Other: not satisfying criteria for high or intermediate risk

9. Type of infection:

(i) Early onset infection (non-contaminant organisms isolated from culture sent before 48 hours):

(a) group B streptococcal disease

(b) other pathogens

(c) indeterminate aetiology

(ii) Late onset infection (non-contaminant organism isolated from culture sent after 48 hours):

(a) gram positive organisms except *coagulase negative staphylococcus*

(b) *coagulase negative staphylococcus*

(c) gram negative organisms

(d) fungal infection

(e) other pathogens

(f) indeterminate aetiology

(iii) Post surgery

10. Type of IVIG. This subgroup analysis will analyse separately babies recruited in hospitals using the different IVIG products included in INIS. This subgroup analysis will include baseline characteristics and treatments after randomisation as well as outcomes.

### Interim analyses: the Data Monitoring and Ethics Committee

For the trial, a Data Monitoring and Ethics Committee (DMEC) has been established. This is independent of the trial organisers and meets at least once per year. During the period of recruitment to the trial, interim analyses are supplied, in strict confidence, to the DMEC, together with any other analyses the DMEC may request. In the light of interim data, and other evidence from relevant studies (including updated overviews of the relevant randomised controlled trials), the DMEC will inform the Trial Steering Committee, if in their view: i) there is proof beyond reasonable doubt that the data indicate that any part of the protocol under investigation is either clearly indicated or contra-indicated, either for all infants or for a particular subgroup of trial participants, or ii) it is evident that no clear outcome will be obtained. Decision to inform the Trial Steering Committee in either of these circumstances will in part be based on statistical considerations.

Appropriate criteria for proof beyond reasonable doubt cannot be specified precisely. A difference of at least 3 standard deviations in the interim analysis of a major endpoint may be needed to justify halting, or modifying, such a study prematurely. If this criterion were to be adopted, it would have the practical advantage that the exact number of interim analyses would be of little importance, and so no fixed schedule is proposed [60].

Unless modification or cessation of the protocol is recommended by the DMEC, the Trial Steering Committee, collaborators and administrative staff (except those who supply the confidential information) will remain ignorant of the results of the interim analysis. Collaborators and all others associated with the study may write through the trial office to the DMEC to draw attention to any concern they may have about the possibility of harm arising from the treatment under study, or about any other matters that may be relevant.

The membership of the Data Monitoring and Ethics Committee is :

[name] (Chair)

[name]

[name]

[name]

[name]

[name]

### Sample Size and Feasibility

Table 4 shows positive blood culture rates (including probable contaminants) in 3,963 consecutive infants of all birthweights admitted to a randomly selected, nationally representative cohort of 54 UK neonatal units between 1st March 1998 and 4th September 1998 in a study of organisation and outcomes of neonatal care funded by the NHS Executive [6].

**Table 4 T4:** Positive blood culture rates

**Number with positive cultures**	**Mortality (all causes)**	**Number with negative cultures**	**Mortality (all causes)**
204/3,963 (5%)	16/204 (8%)	3,759/3,963 (95%)	95/3,759 (2.5%)

Among VLBW infants with positive blood cultures, mortality was 14%. In a North American cohort, mortality in VLBW infants with septicaemia was 21% [7]. Assuming combined rates of mortality and major morbidity of 10–20% for all infants and 20–30% for VLBW infants, Table 5 outlines estimated sample sizes.

**Table 5 T5:** Range of estimated sample sizes

**Mortality or major morbidity in control group**	**Mortality or major morbidity in IVIG group**	**Relative risk reduction**	**Total sample size required to detect difference with 95% confidence**	
			
			**80% power**	**90% power**
30%	26%	13%	4,052	5,392
30%	25%	17%	2,580	3,428
30%	20%	33%	626	824
25%	21%	16%	3,572	4,748
25%	20%	20%	2,266	3,006
25%	15%	40%	540	708
20%	16%	20%	2,994	3,972
20%	15%	25%	1,890	2,502
20%	12.5%	37.5%	810	1,066
15%	12%	20%	4,204	5,582
15%	10%	33%	1,450	1,914
12%	9%	25%	3,408	4,516
10%	7.5%	25%	4,166	5,524

